### Recruitment Procedures for Relatives

In order to alleviate ethical concerns associated with contacting blood relatives (ie, first- and second-degree relatives, and first cousins) without their explicit consent, the CASCADE study will approach them through index cases and will approach only relatives the index case is willing to contact. This recruitment method has been used in previous family-based studies with very good recruitment outcomes [69,70]. Index cases will be mailed recruitment packages to pass on to their relatives, including an information letter, two copies of the informed consent form, two copies of the participation refusal form, and a stamped self-addressed envelope for relatives to return their response to the PI. Relatives’ identifiable information will not be released to the PI. By returning a signed informed consent, the relative indicates willingness to participate and releases their identifiable information to the PI. Once this information is available, a recruiter will contact them to ascertain eligibility. If relatives do not respond after 6 weeks, the PI will contact the index case asking them to pass on a reminder letter to the nonresponding relative. If this effort yields no response, there will be no further attempts to contact the relative. Relatives agreeing to participate will receive a similar survey as the index case, asking if they are willing to (1) invite additional relatives to the CASCADE study, (2) be contacted once a year for 5 years and provide updated information about their health, and (3) participate alone or with a blood relative in a focus group. Relatives can also participate in all or some of the above study steps.

### Recruitment Procedures for Focus Groups

Two series of focus groups will be organized to explore the (1) difficulties associated with patient-provider communication regarding genetic cancer risk, (2) difficulties associated with patient-family communication regarding the pathogenic mutation, (3) mutual influence of patient-provider and patient-family communication, and (4) acceptability of a family-based intervention designed to enhance communication, coping, and decision making for genetic testing. A purposeful sample of index cases and relatives will be selected from individuals who agreed to participate in focus groups. The sampling method will be based on the expertise of the qualitative methodologist from interviews with Swiss *BRCA* carriers [32,33,71] and the PI’s experience conducting focus groups with US *BRCA* families. Segmentation strategy will guide sampling methods and the composition of the focus groups. Each focus group will be relatively homogeneous, while the full set will include several potentially distinct perspectives [72]. Focus groups will include 5-10 participants. Male and female cancer patients and cancer-free individuals will be selected to represent HBOC and LS.

It is expected that data saturation will be reached with 6-10 focus groups including about 30-60 carriers and 30-60 relatives. The first series of focus groups will include only mutation carriers stratified according to level of family communication (high, intermediate, low). These focus groups will explore the difficulties in patient-provider and patient-family communication, and the interrelatedness of these two types of communication. The second series of focus groups will include carriers and relatives and will explore the acceptability of an intervention designed to facilitate communication of test results among family members, helpful coping mechanisms, and decision making for genetic testing. Two sampling methods are envisioned. One method involves several members of the same family who can be invited together; the other involves 3-4 family pairs consisting of one carrier and one relative, which will be homogeneous in terms of gender, health status, etc. The sampling method of the second series of focus groups will be informed by responses to the CASCADE survey and findings from the first series of focus groups.

### Data Collection and Data Management

The CASCADE survey will be developed in English, translated into three languages (German, French, and Italian), and back-translated into English by professional translators, except for scales with validated versions in these languages (eg, 12-Item Short Form Health Survey [SF-12]). Discrepancies will be resolved by the PI with the collaboration of the translators and the co-investigators. Index cases and relatives will be given the choice to complete the CASCADE survey either as paper/pencil or using an online platform. The content of the paper/pencil and online survey are identical. Participants who choose to complete the survey online will receive an access code and will be instructed how to log into a secure Web platform. If a survey is missing important information (eg, number of relatives the index case is willing to contact), research personnel will contact participants to ascertain it.

No identifying information, such as name and address, is collected with paper/pencil or online surveys. Each index case is given a code; for example, G001-IC stands for an index case selected from the Geneva clinic with the family study code 001. Relatives recruited from this index case will be coded G001-R1, G001-R2, etc, to establish the link between family members. This code will be used for surveys, consent forms, refusal forms, and correspondence letters to match participants to the correct family unit and maintain the study’s internal validity. The PI and coordinators will keep logs with these codes. The coding key will be kept in a password-protected computer file and will be available to the PI, members of the Swiss Cancer Genetic Predisposition Cascade Screening Consortium, and key personnel. The code will be broken only to avert an immediate risk to the health of the person, in cases of withdrawal from the study, or when there is a legal basis.

All study data will be collected and stored in a secure database and handled by the data management team from the Clinical Trials Unit, University Hospital, Basel (CTU Basel). The online survey will be implemented using LimeSurvey, installed on a separate server, and exclusively used for the study. Lime Survey is an established app to perform online surveys. The system (server and data) is integrated in a regular backup process. Data transfer from and to the Web-based survey system are encrypted using secure sockets layer/transport layer security (SSL/TLS). The secure database will be used for data collection and to track returned surveys. Data entered for paper/pencil surveys will be double-checked for accuracy. The usability of the paper/pencil or online survey will be assessed based on number of individuals who choose either mode, percent of missing data, etc. Many items are parts of multi-item scales and are anticipated to correlate with each other. The reliability of these scales will be tested using principal component analyses and Cronbach alpha coefficients. Scales with alpha≥.71 will be used. On completion of approximately 30 surveys, scale psychometrics will be examined. For any given scale that shows less than required psychometric properties (ie, Cronbach alpha<.71 and factor analysis indicates item loadings <10% compared to item loadings in the original scale), a revision of the translated scale will be undertaken. This will allow comparisons of scale reliability based on delivery mode and will establish whether the survey can be administered interchangeably.

Health-related and personal data collected for the CASCADE study are confidential; coding will safeguard participants’ confidentiality. All study documents will be archived in the PI’s office. Site-related documents will be archived at the office of each medical director. Administrative data are accessible only by authorized personnel and data managers from CTU Basel. Direct access to documents will be permitted for monitoring, audits, or inspections. Ethics committee members, members of the Swiss Cancer Genetic Predisposition Cascade Screening Consortium, the statistician, and key personnel will have access to project plan, dataset, statistical code, etc, during and after the study (publication, dissemination). Paper/pencil surveys will be stored in a separate research office in the PI’s building for 5 years and then destroyed by shredding. Once all data have been collected, the complete dataset and survey setup will be exported by CTU Basel and transferred to the PI and the statistician via a secure channel. The survey system (including database) will be purged after the end of the study. The PI will archive the electronic data for a minimum of 10 years.

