**Recruitment of eligible index cases**			
	Recruitment package to index cases	The medical director of each clinical site (co-PI or site co-investigator) and the site coordinator mail recruitment packages to index cases. If the index case did not receive genetic counseling at the testing site, then the recruitment package is sent to the referring physician who is asked to pass it on. Three attempts will be made to contact index cases. The medical director will inform treating oncologists about the participation of index cases.	Unique identification coding scheme enabling identifying index cases, site they were recruited from, and type of hereditary cancer syndrome (HBOC or LS). Dates recruitment packages were sent to physicians, dates the response from Index cases was received, and recruitment attempts made.
	Engagement of index cases in the CASCADE study	The site coordinator receives the informed consent or participation refusal form from index cases. Index cases accepting participation receive the CASCADE survey in their preferred language and format (paper/pencil or online) from the PI. The PI creates a coding key for identifying participants and the Clinical Trials Unit creates a coding key for variables assessed in the CASCADE survey.	Identifiable information for index cases accepting participation is passed on from site coordinators to the PI. Response rate from index cases, acceptance to participate in various stages of the CASCADE study, reasons for nonparticipation and preferred language and format for survey.
	Survey from index cases	The PI and the data management team receive the completed survey from index cases either in paper/pencil or online.	Assessment of data quality in each format (eg, percent missing data, outliers). Assessment of instrument reliability (Cronbach alpha and principal component analysis). Number of eligible relatives. Number of eligible relatives the index case is willing to invite. Characteristics of relatives reported by the index case. CASCADE study outcomes.

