### Data Analyses

Selection bias will be minimized by random selection of mutation-harboring families in each clinical site from three linguistic regions of Switzerland. Stratification will ensure selection of an equal proportion of index cases from clinical sites that offer genetic services for both syndromes. The study will try to recruit all index cases from clinical sites including fewer than 100 mutation-harboring HBOC/LS families to ensure a representative sample.

All statistical analyses will be conducted in licensed software packages, including Microsoft Excel, SPSS (IBM), and R. For all statistical tests, significance will be set at two-sided alpha=.05. Data values will be examined for legality (within appropriate range) using histograms and box plots and corrected when possible. Descriptive analyses will include calculating means, standard deviations, frequencies, and percentages of variables and participant descriptors. Bivariate analyses (Pearson correlations, chi-square test for differences in proportions, and *t* test for differences in means) will assess associations between demographics and clinical characteristics. Regression analyses will incorporate generalized estimating equations for pairing index cases with their relatives and explore to what extent predictors are in direct, mediating, or moderating relationship to an outcome.

The following comparisons will take place: between index cases and relatives, between HBOC and LS, between men and women, cancer patients versus cancer-free individuals, participants with children versus those with no children, between different age groups and different cancer diagnoses. Data from participants who withdraw will be kept in the study to ensure the internal validity of the study. Missing data from multi-item scales will be addressed with multiple imputations using R software if they exceed 5% of observations and if they are less than 25% for each specific scale. Scale reliability will be assessed with Cronbach alpha and principle component analyses. Deviations from the planned analyses are not foreseen. The study statistician will review and approve any deviations from the original statistical plan if necessary.

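### Equal scale reliability on paper and online cannot establish that the two survey modes are interchangeable

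*Protocol article*

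**What the plan says.** All statements are in the protocol article.

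- **Choice of mode** (Data Collection and Data Management): "Index cases and relatives will be given the choice to complete the CASCADE survey either as paper/pencil or using an online platform". Both formats are said to have identical content.
- **Reliability tools** (same section): "The reliability of these scales will be tested using principal component analyses and Cronbach alpha coefficients". The threshold follows: "Scales with alpha≥.71 will be used".
- **Early look** (same section): "On completion of approximately 30 surveys, scale psychometrics will be examined". Poor alpha and loadings trigger revision of a translated scale.
- **Conclusion about mode** (same section): "This will allow comparisons of scale reliability based on delivery mode and will establish whether the survey can be administered interchangeably".
- **Other checks by mode**: Table 1 lists "Assessment of data quality in each format (eg, percent missing data, outliers") for index cases and the same for relatives. Data Collection and Data Management and Outcomes add uptake of each format and missing data. None of the checks named compares scores between modes.
- **Planned contrasts** (Data Analyses): "between index cases and relatives, between HBOC and LS, between men and women, cancer patients versus cancer-free individuals", then participants with and without children, age groups and cancer diagnoses. Regressions use generalized estimating equations (GEE) for family pairing. No covariates are named.

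**The concern.** The article names a criterion, reliability compared by mode, and says that it will settle whether the modes are interchangeable. Interchangeability asks whether a person would give the same score on paper as online. Reliability asks whether the items of a scale hang together within a mode. A scale can be equally reliable in both modes while one mode reads systematically higher, so the criterion can be followed exactly and still not support its conclusion.

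This matters because mode is self-selected. If online use differs between groups that the study compares, with age groups the obvious candidate, a mode shift would appear as a group difference.

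**Working it through.** The plan states no figure for mode equivalence, so there is none to reproduce.

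**1. Does the criterion respond to a shift?** For k items, alpha = k/(k−1) × (1 − sum of item variances / variance of the total). Adding a constant to every item leaves each variance and covariance unchanged, so alpha, loadings and eigenvalues are unchanged too. Numerical check on a simulated 10-item scale (inter-item correlation 0.35, 300 respondents), with 0.5 points added to every item in the second mode:

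| | Mode 1 | Mode 2 (shifted) |
|---|---|---|
| Cronbach alpha | 0.8187 | 0.8187 |
| First eigenvalue | 3.814 | 3.814 |

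Stacking the two modes gives alpha 0.846, so across pooled data the shift even looks like better reliability. The invariance is algebraic and does not depend on sample size.

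**2. Which outcomes does the criterion not reach?** Table 2 includes perceived cancer risk (1 item), self-efficacy for using genetic services (1 item, relatives) and whether genetic testing was done (one yes/no question). A single item has no alpha and no loadings, so for these the criterion has no content, although the conclusion is drawn for the whole survey.

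**3. What could an undetected shift do to a group contrast?** If one mode moves scores by d SD in both groups, and the groups differ by Δp in their share of that mode:

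bias = d × Δp

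Example: 305 index cases against 381 relatives (Sample and Sample Size; 305 × 2.5 × 0.5 = 381.25).

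SE = √(1/305 + 1/381) = 0.0768 SD

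False-positive rate = Φ(bias/SE − 1.96) + Φ(−bias/SE − 1.96)

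The values of d and Δp are assumptions. The test is two-sided at 0.05 and observations are treated as independent.

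| Δp | d = 0.2 SD | d = 0.3 SD | d = 0.5 SD |
|---|---|---|---|
| 0 points | 0.050 | 0.050 | 0.050 |
| 20 points | 0.082 | 0.122 | 0.256 |
| 30 points | 0.122 | 0.216 | 0.497 |
| 40 points | 0.180 | 0.345 | 0.740 |

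Worked cell: d = 0.3 and Δp = 0.20 give bias 0.06 SD, bias/SE = 0.78 and a rate of 0.122.

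**4. Can the study look at scores directly?** The total is 305 + 381 = 686, or 343 per mode if the split is even (assumed). A comparison of mode means then has power 0.75 for a 0.2 SD shift and 0.98 for 0.3 SD. At the early look, with 15 per mode, power is 0.08 and 0.13. The comparison belongs in the full dataset.

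**5. Would a formal equivalence margin work?** Take ±0.2 SD as an illustration. With 343 per mode the 95% CI half-width is 1.96 × √(2/343) = 0.150 SD. With zero true difference, the interval lies inside the margin only if the estimate is within 0.050 SD of zero, a chance of about 49%. For scales given only to index cases the half-width is 1.96 × √(4/305) = 0.22 SD. For scales given only to relatives it is 1.96 × √(4/381) = 0.201 SD. Both exceed the margin, so those scales could never pass.

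**The case against.** The strongest reply is that the article promises only a reliability comparison by mode. The 0.71 threshold governs whether a scale is used, and alpha with loadings governs revision of a translation. Neither is given as a pass mark for mode. On this view the fault is a verb: reliability informs the question and does not establish the answer.

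Much of this stands, and it limits the finding in four ways.

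- A reader might infer that the study will declare the modes interchangeable whatever the mode effect is. The documents do not support that. They give no decision rule, and only a uniform shift is invisible. A mode that changed item variances, correlations or loadings could be noticed.
- A reader might infer that the modes will be pooled without adjustment. The article does not say so. It names no regression covariates, so the absence of mode tells us nothing, and the analysis plan, which is not shown, may adjust for it. The listed checks by mode are also worded as examples.
- The false-positive rates rest on assumed shifts and mode shares. With no shift, or with equal shares, there is no bias.
- Because mode is chosen, even an adjusted paper-online difference mixes mode effect with residual selection.

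The reply does not rescue the sentence itself. It draws a firm conclusion from a quantity that cannot bear it. Identical content does not show identical responding, and a later covariate would not make the criterion valid.

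**Conclusion.** The concern holds for the criterion as stated. Comparing Cronbach alpha and component structure by delivery mode cannot establish interchangeability at any sample size, because these statistics do not respond to a uniform score shift and do not exist for single-item outcomes. This part needs no assumptions.

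The effect on results is conditional. It requires both a mode shift and unequal mode shares between the groups compared. For assumed shifts of 0.2 to 0.5 SD and share differences of 20 to 40 points, the false-positive rate runs from about 8% to 74%, using a normal approximation, the planned 305 and 381 participants, a shift common to both groups and no family clustering. The point is worth correcting because mode is already recorded and the correction is cheap.

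**What to change.** 1. Reword the sentence in Data Collection and Data Management: reliability by mode describes reliability only and does not establish interchangeability.
2. On the full sample, report for each scale the paper-online mean difference with its 95% CI, from a GEE model adjusted for age, sex, language, education, index/relative role and cancer status. State that residual confounding remains because participants choose their mode.
3. Repeat the main group comparisons in Data Analyses with delivery mode as a covariate and show both sets of results.
4. Do not impose a ±0.2 SD equivalence margin, which this sample is too small to meet reliably. Let readers judge the intervals.

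The cost is one extra covariate, one additional table and no new data collection. The downside is a weaker statement about interchangeability, possibly inconclusive for some scales, above all those given only to index cases or only to relatives.

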### Outcomes

Table 2 [73-89] describes primary outcomes for index cases and relatives and the scales used to assess them. The feasibility of establishing a family-based registry will be assessed using the number of mutation-harboring families associated with HBOC and LS from each clinical site, the number of relatives identified from pedigrees and family history, index cases’ response rate to the CASCADE survey, the number of relatives each index case is willing to invite, relatives’ response rate to the CASCADE survey, and the willingness of index cases and relatives to be contacted once a year for 5 years. Additional outcomes include assessing acceptance rates of paper/pencil and online platform and quality of data (eg, percent missing values).

**Table 2 table2:** Scales used in the CASCADE survey.

Concepts		Scale	Index case	Relatives
Demographics		Age, gender, education, employment status (previously used) [73]	√	√
**Health history**				
	Comorbidities	Chronic conditions associated with mobility, cardiovascular disease, diabetes, anxiety, depression Self-reported list (yes/no) (previously used) [73]	√	√
	Reproductive history (females)	Risk factors associated with the Gail model [74,75] Self-reported	√	√
	Alcohol, tobacco, physical activity	Self-reported (previously used) [76]	√	√
**Cancer-related**				
	Cancer diagnoses	Type of cancer, age of onset Self-reported list (previously used) [73]	√	√
	Surgery	Surgeries associated with HBOC & LS Prophylactic surgeries Self-reported (previously used) [29]	√	√
	Surveillance behaviors	Surveillance for cancers associated with HBOC & LS Surveillance for common cancers Investigating tool developed per the American Society of Clinical Oncology guidelines [77] (previously used) [73]	√	√
		Barriers & facilitators (previously used) [73] Coordination of medical care (multiple choices) High out-of-pocket costs (yes/no)	√	√
	Family history	Family history in 1st and 2nd degree relatives & 1st cousins – type of cancer, age of onset (previously used) [73]	√	√
**Psychosocial needs**				
	Fear of cancer recurrence	Concerns About Recurrence Scale [78] 4 items, 7-point Likert scale	√	√
	Perceived cancer risk	Perceived Risk for Developing Cancer [79] 1 item, 10 points with verbal anchors	√	√
	Decisional conflict	Decisional Conflict associated with genetic testing [80] 16 items, 7-point Likert scale		√
	Decisional regret	Decisional Regret associated with genetic testing [81] 5 items, 7-point Likert scale	√	
	Coping with stressful events	Brief Cope [82] 25 items, 7-point Likert scale	√	√
	Self-efficacy	Self-efficacy dealing with cancer [83] 14 items, 7-point Likert scale	√	√
		Self-efficacy – use genetic services (counseling & testing) [83] 1 item, 7-point Likert scale		√
	Knowledge	Breast & Ovarian Cancer Risk Factor Knowledge Index [84,85] 17 items (True, False, Don’t Know)	√	√
		Knowledge of Breast Cancer Genetics Scale [70] 12 items (True, False, Don’t Know)	√	√
		LS Risk Factors & Inheritance Investigator developed 19 items (True, False, Don’t Know)	√	√

